**Study Flow Chart**

| **Study Phase** | **Screening period** | | **Treatment period (every 3 weeks (21 days) as one treatment cycle)** | | | **Study treatment discontinuation** | **Follow-up period** |
| --- | --- | --- | --- | --- | --- | --- | --- |
|  |  |  | **Neoadjuvant therapy** | | **Surgery** |  |  |
| **Treatment cycle/visit name** | Screening period | | Cycle 1 | Cycles 2–3 | Surgery | Study treatment discontinuation | Follow-up of events |
| **Visit time** |  | |  | |  | Becoming aware of or confirming the discontinuation of study treatment | 1 year after surgery: every 3 months  1–2 years after surgery: every 6 months |
| **Window period (days)^1^** | -28 to -8 | -7 to -1 |  | ±3 | ±7 | ±7 | 1 year after surgery: ±7  1–2 years after surgery: ±15 |
| Informed consent form | **X** | |  |  |  |  |  |
| Inclusion and exclusion criteria | **X** | |  |  |  |  |  |
| Demographics and medical history | **X** | |  |  |  |  |  |
| Prior treatment and concomitant treatment**^2^** | **X** | |  | **X** | **X** | **X** |  |
| Height, weight, and vital signs**^3^** | **X** | |  |  |  |  |  |
| Adverse events**^4^** | **X** | | **X** | **X** | **X** | **X** |  |
| Echocardiography | **X** | |  |  |  |  |  |
| 12-lead electrocardiogram | **X** | |  |  | **X** |  |  |
| Complete physical examination | **X** | |  |  |  |  |  |
| Symptom-directed physical examination | **X** | | **X** | **X** | **X** | **X** |  |
| ECOG score |  | **X** | **X** | **X** | **X** | **X** |  |
| Gastroscopy**^5^** | **X** | |  |  |  |  |  |
| PD-L1 expression (CPS score)**^6^** | **X** | |  |  |  |  |  |
| MSI status**^7^** | **X** | |  |  |  |  |  |
| Subsequent anti-tumor treatment |  | |  |  |  |  | **X** |
| Survival status |  | | **X** | **X** | **X** | **X** | **X** |
| Serplulimab**^8^** |  | | **X** | **X** |  |  |  |
| Oxaliplatin + Tegafur (SOX)**^9^** |  | | **X** | **X** |  |  |  |
| Thymalfasin**^10^** |  | | **X** | **X** |  |  |  |
| Hematology, biochemistry, coagulation, urinalysis**^11^** |  | **X** | **X** | **X** | **X** |  |  |
| Thyroid function**^12^** |  | **X** | **X** | **X** | **X** |  |  |
| Cardiac function markers**^13^** |  | **X** | **X** | **X** | **X** |  |  |
| Tumor markers**^14^** |  | **X** | **X** | **X** | **X** |  |  |
| Pre-transfusion eight-item panel**^15^** |  | **X** |  |  |  |  |  |
| Postoperative pathological examination |  | |  |  | **X** |  |  |
| Imaging examination**^16^** | **X** | |  | **X** | **X** |  | **X** |

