- Disease-free Survival (DFS): Disease-free survival refers to the time from the start of randomization to disease recurrence or death due to disease progression. DFS will be defined as the last date the patient is last confirmed to be disease-free survival if the patient does not experience disease progression during the study. Patients who discontinue the trial for reasons other than disease progression (no subsequent imaging) and patients who receive treatment after the trial will be censored at the time of discontinuation or the time of initiation treatment after the trial. When patients are not censored at the time of discontinuation from the trial or the time of initiation treatment after the trial, pre-planned sensitivity statistical analyses will further confirm DFS based only on the time of event of radiologically confirmed progression. New onset of other tumors are not considered as disease progression events and are not censored. If an imaging examination and evaluation show disease progression, the date of disease progression will not be the imaging examination date when disease progression is first shown, but the imaging examination date when disease progression is clearly confirmed. If disease progression is diagnosed by other clinical modalities, the date of diagnosis will be used as the date of disease progression.
- Overall Survival (OS): Overall survival refers to the date from enrollment to death due to any cause. For patients who are alive at last follow-up, their OS will be censored based on the time of last follow-up. For patients who are lost to follow-up, their OS will be censored based on the last confirmed survival time before loss to follow-up. The OS of data censor is defined as the time from enrollment to censoring.
- R0 resection rate: R0 resection rate refers to the proportion of patients who complete R0 resection in the total number of enrolled patients with surgically resectable gastric cancer through 3 cycles (21 days per cycle) of treatment with Serplulimab in combination with SOX regimen and 9 weeks of thymalfasin. Of these, R0 resection refers to negative microscopic margins.

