**Body surface area (m^2^), first dose (as Tegafur):**

<1.25 m^2^, 40 mg/dose

≥1.25 m^2^ to <1.5 m^2^, 50 mg/dose

≥1.5 m^2^, 60 mg/dose

- 1. **Postoperative Follow-up Period**

1. The occurrence of postoperative complications should be followed up within 30 days after surgery;
2. All enrolled subjects will be continuously monitored: patients who receive surgery will be followed up every 3 months within the first year after surgery and every 6 months thereafter until 2 years, with the following recorded: physical examination, laboratory test results (including tumor marker tests), imaging findings (presence of recurrence or metastasis), adjuvant treatment regimens, and treatment duration.
3. **Use of Study Drugs**
   1. **Serplulimab**

Serplulimab from Shanghai Henlius Biotech, Inc. is used in this study, with a strength of 100 mg/vial. The main active ingredient of Serplulimab is a recombinant fully human anti-programmed death receptor-1 (PD-1) monoclonal antibody, with a concentration of 10 mg/mL. This product is a clear, colorless liquid, free from foreign matter, flocculent material or precipitate. The excipients include citric acid, sodium citrate, sodium chloride, mannitol, polysorbate 80, and water for injection.

The finished product of Serplulimab should be stored protected from light at 2–8℃, with a shelf life of 36 months. If turbidity, precipitation, or other quality issues are observed in the injection solution, the product should be immediately stored in sealed containers and Henlius should be notified immediately.

The intravenous infusion time of Serplulimab should be 30–60 minutes. Do not administer by intravenous bolus or a single rapid intravenous injection. Dilution instructions for the drug prior to administration are as follows:

- Prepare the solution and perform infusion
- Do not shake the vial.
- Allow the vial to return to room temperature (25°C or below) before use.
- After taking it out of the refrigerator, the vial may be stored at room temperature (25°C or below) for up to 24 hours prior to dilution.
- Visually inspect the solution for injection for particulate matter and discoloration prior to administration. This product is a clear to slightly opalescent, colorless to pale yellow liquid, free from foreign matter. If visible particles are observed, the vial should be discarded.

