Imaging examinations will be performed to evaluate efficacy and feasibility of surgery after the completion of Cycles 2 and 3 of neoadjuvant therapy (within 7 days before the start of Cycle 3 and within 7 days after the end of Cycle 3). Imaging examinations are conducted after surgery and prior to adjuvant therapy, and pathological assessment will also be performed to evaluate the completeness of surgery. Evaluation requires a full abdominal direct contrast-enhanced (iodinated contrast) CT scan and gastric tumor MRI (contrast-enhanced). The same imaging technique should be used for pre- and post-evaluation in the same patient, and all imaging data must be retained. Patients who experience PD may continue the study treatment if they are willing and deemed suitable by the investigator to continue the original treatment regimen after re-signing the informed consent form, and re-evaluation will be performed after 4 weeks; otherwise, the patients will discontinue the study. For patients who discontinue treatment due to intolerable toxicity, if no efficacy evaluation is performed within 4 weeks prior to discontinuation, an efficacy evaluation should be conducted at the time of discontinuation.

For patients with potentially resectable gastric cancer after neoadjuvant therapy, surgery is scheduled within Weeks 2–6 after the completion of the last chemotherapy + immunotherapy. The surgical approach is determined based on the degree of disease response, including R0 resection, R1 resection, or cytoreductive surgery. The postoperative efficacy evaluation criteria primarily focus on surgical pathological assessment (complete pathological response rate, major pathological response rate, tumor regression grade, R0 resection rate, etc.), supplemented by imaging evaluation (objective response rate, disease control rate) for reference. At this point, the study has achieved its primary endpoint.

1. **Safety Reports and Adverse Event Management**
   1. **Definition of Adverse Event**

An adverse event (AE) is defined as any unfavorable and unintended medical occurrence in a clinical study participant from the time of signing the informed consent form, whether or not considered related to the study drug. AEs include, but are not limited to, the following circumstances:

- Exacerbation of pre-existing (prior to entering the clinical trial) medical conditions/diseases (including exacerbation of symptoms, signs, and abnormal laboratory findings);

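### Overall survival starts at enrollment, but an enrolled patient who never has surgery has no dated survival contact after treatment stops

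*Protocol*

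**What the plan says.** **Endpoint.** Section 2.2 states: "Overall survival refers to the date from enrollment to death due to any cause". The synopsis agrees. Two censoring rules follow: "For patients who are alive at last follow-up, their OS will be censored based on the time of last follow-up", and "For patients who are lost to follow-up, their OS will be censored based on the last confirmed survival time before loss to follow-up". Section 12.3 plans a Kaplan-Meier OS curve with a 95% confidence interval and no hypothesis test specific to OS. The planned size is 30 patients in one arm.

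**Follow-up calendar.** Section 6.3 begins "All enrolled subjects will be continuously monitored" and continues, after a colon, "patients who receive surgery will be followed up every 3 months within the first year after surgery", then at 6-month intervals up to 2 years. The flow chart dates its follow-up column from surgery as well ("1 year after surgery: every 3 months"), and so does the synopsis. Section 3 describes follow-up after surgery as the source of disease-free survival and OS.

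**Before and at discontinuation.** The flow chart marks survival status at Cycle 1, Cycles 2–3, surgery, study treatment discontinuation and follow-up. The discontinuation visit is a single visit, held when the site learns of or confirms the discontinuation.

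**Progression.** Section 10 allows a patient with progressive disease to continue after re-consent if the investigator agrees; "otherwise, the patients will discontinue the study". Section 5.1 lists progression with loss of eligibility for radical resection as a termination criterion. It exempts progression that remains resectable after at least one completed cycle.

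**Deaths.** Section 11.4 (Death) requires deaths during the whole study, including the 30 days after the last dose, to go on a death report form. This includes deaths from tumor progression.

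**The concern.** OS covers everyone enrolled, but the calendar that supplies its data after treatment starts from an event that some patients never reach. A patient who becomes unresectable, stops for toxicity or declines surgery has no date from which to count visits, no interval and no end of follow-up. The last dated check is the discontinuation visit, and the censoring rules then place that patient's OS time at about that point unless later information happens to arrive.

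Kaplan-Meier estimation assumes that patients censored at a given time have the same future risk as those who remain. Patients who fail neoadjuvant treatment probably have a higher risk of death than those who reach resection. Removing them early would leave a curve that mainly describes resected patients but is labelled as OS from enrollment for the whole regimen. The error would grow with the share of patients who fail to reach surgery. An analysis plan cannot repair this later, because the contacts would not have been made.

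**Working it through.** The protocol gives no OS rate, event count or non-resection rate, so it has no figure to reproduce. The check has two parts.

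**1. Does any passage give an unoperated patient a dated contact after discontinuation?**

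| Place | What it gives an unoperated patient |
|---|---|
| Section 6.3, opening clause | Monitoring, with no interval, duration or content |
| Section 6.3, schedule | Nothing: limited to patients who have surgery |
| Synopsis; flow chart, follow-up column | Nothing datable: counted from surgery |
| Flow chart, survival status row | Checks up to and including the discontinuation visit |
| Section 10 | Exit from the study for a progressing patient who does not continue treatment |
| Section 11.4 (Death) | Recording of deaths during the study; not clearly extended to patients who have left it |

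None does.

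**2. How large could the effect be?**

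All inputs are assumptions, apart from N = 30, which is used to turn shares into patients:
- Exponential survival in each group.
- A share f of patients is not operated. All of them are censored at month 3, with no later death captured.
- Operated patients are followed fully.
- S_op(24) is 70% or 80%; median survival of unoperated patients is 8, 12 or 18 months.

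Month 3 is plausible. Cycle 3 starts on day 43 (1 + 2×21) and three cycles end on day 63. A surgery window of 2–6 weeks therefore runs from day 57 (43 + 14) at the earliest reading to day 105 (63 + 42) at the latest.

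Formulas:
- True value: S_mix(24) = (1 − f)·S_op(24) + f·S_non(24)
- Kaplan-Meier in large samples under this censoring: KM(24) = S_mix(3) × S_op(24) / S_op(3)

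One case in full, with f = 10% (3 of 30), S_op(24) = 0.70 and unoperated median 12 months:
- S_op(3) = 0.70^(3/24) = 0.956; S_non(3) = 0.5^(3/12) = 0.841
- S_mix(3) = 0.9×0.956 + 0.1×0.841 = 0.945
- KM(24) = 0.945 × 0.70/0.956 = 0.692
- True: 0.9×0.70 + 0.1×0.25 = 0.655
- Overstatement: 3.7 percentage points

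Range over the grid:

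| Share not operated | Patients of 30 | Overstatement at 24 months (points) |
|---|---|---|
| 5% | 1–2 | 1.3 to 2.5 |
| 10% | 3 | 2.6 to 5.1 |
| 20% | 6 | 5.1 to 10.2 |

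If unoperated patients have the same hazard as operated patients, the overstatement is 0.

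A second set of assumptions (2-year OS 75% if resected, 20% if not, censoring at 3 months) gives S(3) = 0.75^(1/8) = 0.965 and 0.20^(1/8) = 0.818. With 4 of 30 unresected, KM = 0.945 × 0.75/0.965 = 0.735 against a true (26×0.75 + 4×0.20)/30 = 0.677. With 2 it is 0.742 against 0.713, and with 6 it is 0.727 against 0.640. The overstatement is about 3, 6 and 9 points for 2, 4 and 6 patients, which agrees with the grid.

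**The case against.** The strongest reply is that the commitment to follow everyone is already in the protocol and only an interval is missing.

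- **Monitoring and survival status.** Section 6.3 names all enrolled subjects, and the flow chart collects survival status before surgery and at discontinuation. This stands against any reading that survival is collected only from surgery. It does not supply a dated contact after discontinuation.
- **Deaths.** Section 11.4 does not make death recording depend on surgery. If sites apply it to unoperated patients throughout, the bias disappears. Its reach depends on whether a patient who has discontinued under Section 10 is still in the study, which the protocol leaves unclear.
- **Stopping versus withdrawing.** Section 5.2 does not list progression among the withdrawal criteria, and several items in 5.1 concern treatment. Section 10 could therefore be read as ending treatment only. But its words refer to the study, and 5.1 itself speaks of study termination when it exempts resectable progression. Both readings remain open, and that is the defect.
- **Not every progressing patient is affected.** Some continue after re-consent, and some go to surgery and enter the dated schedule. This stands.
- **Limited consequence.** OS is secondary and descriptive. Near 68% survival with 30 patients, the simple binomial 95% half-width is 1.96×√(0.68×0.32/30), about 17 points, which is larger than any bias shown. This stands as a limit on importance. It does not excuse the gap: the bias adds to sampling error and does not show in the confidence interval.

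A reader might infer that OS will lose these patients and is certainly biased upward. The documents do not support that. The effect depends on how many patients go unoperated, on their hazard, and on whether their deaths are captured, and the protocol quantifies none of these.

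**Conclusion.** The point holds as a gap in the follow-up schedule and an inconsistency between sections. OS counts every enrolled patient from enrollment, yet no passage gives a patient without surgery a dated survival contact after treatment discontinuation, and Section 10 can be read as ending that patient's participation. Censoring near discontinuation would then probably be informative, with overstatement of OS as the likely direction. The size of about 1 to 10 points at 24 months assumes 5% to 20% unoperated, a higher hazard in that group, censoring at month 3, and no later deaths captured. The pathologic complete response rate does not depend on this follow-up. The change should be made because it is cheap and cannot be made after the fact, but it does not threaten the trial's main result.

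**What to change.** 1. In Section 6.3, the synopsis and the flow chart, give every enrolled patient who has not withdrawn consent a dated survival-status contact every 3 months in year 1 and every 6 months in year 2. Count from surgery for operated patients, as now, and from treatment discontinuation for those without surgery. A telephone contact is enough.
2. Reconcile Section 10 with Sections 5.1, 5.2, 6.3 and 11.4 (Death), so that stopping study treatment does not by itself end survival follow-up, and so that death recording clearly covers patients who have stopped treatment.
3. Leave the OS censoring rules in Section 2.2 as they are. They already censor at last follow-up or last confirmed survival, and only need the contacts that make those dates current.

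The cost is protocol wording and a few telephone contacts for a handful of patients. No procedure or patient is added, and no treatment decision changes.
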